## A. Basic project data

- Project Title:

**Functional, neuroplastic and biomechanical changes induced by early Hand and Arm Bimanual Intensive Therapy Including Lower Extremities (HABIT-ILE) in pre-school children with uni-and-bilateral cerebral palsy: a European project**

- Project acronym: **Early HABIT-ILE**
- Duration of the project (months): 48 months
- Project Summary (max. 4000 characters including spaces)

An urgent priority in the field of paediatric neurorehabilitation is the development of **effective early motor interventions**. Animal studies strongly suggest early intensive rehabilitation may have a large impact on brain and corticospinal organisation, reducing motor impairments and their mid- to long-term consequences in children with cerebral (CP). Although most brain growth, development and organization occurs within the first 2 years of life, the majority of research into the effectiveness of intensive rehabilitation and mechanisms that underlie responses to therapy has been conducted in school-age children (i.e. > 6 years). Furthermore the main focus of research has been on children with unilateral CP, despite the fact that bilateral CP is the most prevalent form. **Studies of the effectiveness of early intensive interventions on global motor function in larger groups of children with CP, including bilateral CP are thus required.**

Hand and Arm Bimanual Intensive Therapy Including Lower Extremities (**HABIT-ILE**) applies the concepts of motor skill learning and intensive training to both the upper (UE) and lower extremities (LE) and has been shown to improve aspects of motor function of the UE and LE in school age children with unilateral and bilateral cerebral palsy across the 3 levels of the International Classification of Functioning, Disability and Health (ICF). **The principles and content of HABIT-ILE can be applied to pre-school children and this method is highly promising for early rehabilitation.**

The primary objectives of this study are to evaluate the effect of **two weeks of early HABIT-ILE on bimanual performance** in pre-school children with unilateral CP (Randomized Controlled Trial 1=RCT1, N=50 children) and on **gross motor function** of children with bilateral CP (RCT 2, N= 50 children), in comparison with two weeks of **usual motor activity including usual rehabilitation (control group)**. The primary outcome measures will be the difference in Assistive Hand Assessment (**AHA**) and Gross Motor Function Measure (**GMFM**) between base line and at three months.

The network involved in the Early HABIT-ILE project will provide a means for rapid dissemination of the results to clinical centres in French speaking countries, Europe and then world-wide. The early increase in autonomy and reduction of the mid-term consequences of CP is very likely to reduce **the economic cost and societal impact of “cerebral palsy”** at the level of the health care systems. Furthermore, the model of early intensive therapy proposed differs greatly from current rehabilitation standards in many countries. The results of this study should provide high evidence for changing, not only current models of motor rehabilitation in children with CP, but **health policies**, leading to a **new era of early rehabilitation for children with CP**.

### 1. Proposal's context

Cerebral palsy (CP) affects between 2 and 3.6 out of 1000 live births. It causes abnormal patterns of movement and posture, and cognitive and sensory function may also be impaired. These impairments result from structural abnormalities in the brain that occur at different periods of brain development, affecting different processes such as neuronal migration, differentiation, neuronal growth and myelination. Therefore, the timing, extent and location of the central damage impact the subsequent global functioning

of the brain. Symptoms are generally apparent before 18 months of age and the diagnosis is generally confirmed between 13 and 19 months of age. Because CP-related motor deficits have an impact on activity level and autonomy, particular attention has been paid over the last 15 years to interventions for the treatment of motor dysfunctions. **The development of effective early motor rehabilitation is considered an urgent priority in the field of pediatric neurorehabilitation.** Intensive, activity-based, goal-directed interventions have been shown to effectively improve motor function in school-age children with CP. **Although the major brain growth, development and organization occurs within the first 2 years of life, the majority of research into the effectiveness of intensive rehabilitation and mechanisms that underlie responses to therapy has been conducted in school aged children (i.e. > 6 years)**. It is thus crucial to evaluate the effects of intensive rehabilitation in pre-school children, both at a functional and at a cortical level since animal models suggest that such interventions may prevent the development of secondary damage, positively impacting the whole developmental curve of the children.

Animal models of cerebral palsy have shown that the impairments that occur following perinatal brain injury are mainly the result of persistent inflammation, causing alterations in neurogenesis, axonal growth and synaptogenesis, as well as an important deficit in the myelination of white matter due to an alteration in the oligodendrocyte and its precursors. These white matter impairments are likely the cause of a wide range of brain dysfunctions in children with cerebral palsy and contribute to alterations in neuronal activity. **Animal studies have suggested that the generation and maturation of oligodendrocytes is activity dependent** and that the acquisition of a new motor skill increases the generation of oligodendrocytes and oligodendrocyte precursors only 2 hours after the initiation of the motor training. This remarkably fast oligodendrocyte production, along with the rapid increase in the number and size of dendritic spines (synaptic plasticity) with activity, **suggest that an intervention based on motor skill learning may contribute to improve white matter myelination and thus brain function.**

The organization/**structure** of the corticospinal tract (CST) is also affected by the initial brain lesions, with persistence of ipsilateral projections rather than the development of contralateral projections, likely due to the lack of motor activity of the paretic limb. Rodent model studies have shown that motor skill learning modifies the white matter fractional anisotropy, **meaning that the improvement in the quality of the CST is also activity-dependent**. Previous studies based on the timing of motor evoked potential response in babies suggest that the CST system is organized during the first two years of life. **This time period may thus be a window of opportunity during which early stimulation may positively impact CST reorganization**. These topographic changes are due to activity-dependent competition between developing cortico-spinal terminals and other spinal neural systems. This damage secondary to the initial brain lesions can be reversed in kittens by providing intensive motor skill training to the impaired forelimb. **If provided in a window of opportunity, intensive use of affected forelimb in kittens drives a rebalance in the development of synaptic projections**. In human beings the window of opportunity during which these projections might be rebalanced through motor stimulation is not well defined. It is generally assumed to occur during early infancy, probably until the age of two, during the main period of CST fibre myelination. **These arguments from animal and human studies suggest that early motor skill learning based interventions should allow better development of CS projections and thus prevent secondary motor damage at the level of the CST.**

**Compared to the available literature in animals, only a few motor intensive intervention trials have been carried out in very young children and, to our knowledge all have focused on children with unilateral CP.** They evaluated modified forms of constraint-induced movement therapy (CIMT). An adapted baby-CIMT procedure for infants (<12 months) was proposed by Eliasson and colleagues. Another adapted CIMT trial was performed in children between 2 and 3 years of age. In addition, 2 research teams tested the effectiveness of CIMT in children with unilateral CP between the ages of 1 and 6 years and a research team tested the feasibility of carrying out bimanual training in children aged 2 to 4 years. The results of these studies provided moderate evidence about the application of CIMT or bimanual training in young children with unilateral CP. Higher daily intensities of training (Taub et al. and DeLuca et al.: 6 hours per day for a total of 60 hours) seemed to induce larger changes than lower intensity training (Eliasson et al. and Nordstarand et al.: 30 min per day, 6 days a week, for a total of 36 hours; Ferre et al.: 2 hours a day, 5 days a week for 9 weeks), though comparison of results is hindered by differences in the ages of the samples and the use of different assessment tools. All the interventions proposed focused solely on the upper extremity (UE) of children with unilateral CP, despite the fact that the lower extremity (LE) is commonly affected. **The next step in the development of early intensive interventions is to evaluate the effectiveness of therapy which targets global motor function, including the lower extremities, in larger group of children with CP, including bilateral CP.**

[name] (member of the project consortium) and her team designed an intervention for school-age children with unilateral and bilateral CP a few years ago to address both UE and LE deficits. **Hand and Arm Bimanual Intensive Therapy Including Lower Extremities (HABIT-ILE) applies the concepts of motor skill learning and intensive training to both the UE and LE.** It involves stimulation of the UE and LE during combined activities for many hours each day for a period of 2 weeks. **This method has been shown to improve aspects of motor function of the UE and LE in children with unilateral and bilateral cerebral palsy across the 3 levels of the International Classification of Functioning, Disability and Health (ICF):** body function and structures (e.g. strength and dexterity), activity (activities of daily living) and social participation (achievement of personal goals). In addition, recent findings indicate that intensive motor interventions such as HABIT-ILE have a positive impact on executive functions of school-age children with CP (Araneda et al., work in process). Furthermore, HABIT-ILE has been shown to improve the quality of CST fibers in children with CP (increase in the fractional anisotropy values) ([name] et al., submitted). Moreover, the increase in fractional anisotropy was correlated with motor improvements in the hand. **The principles and content of HABIT-ILE can be easily adapted and applied to pre-school children and this method is highly promising for early rehabilitation.**

**To summarize, animal studies strongly suggest early intensive rehabilitation may have an important impact on brain and corticospinal organisation, reducing impairments in children with CP. Studies that target both the UE and LE in pre-school children with both unilateral and bilateral CP are lacking and the timing of the window of opportunity for interventions to prevent secondary damage in children is yet unknown. A more accurate understanding would lead to guidelines for early rehabilitation.**

Summary table of persons involved in the project:

## 2.3. Research Plan

### *Participants*

**One hundred** pre-school children with cerebral palsy (**50 unilateral** for RCT1 and **50 bilateral** for RCT2) will be included. Based on previous intensive motor skill learning trials in school-age children, the **inclusion criteria** will be: children with cerebral palsy (spastic or dyskinetic), unilateral or bilateral cerebral palsy, age 1 to 4 years inclusive (corrected age if preterm birth) and ability to follow instructions and complete testing according to the age. **Exclusion criteria** will be epilepsy, botulinum toxin injections or orthopedic surgery within the past six months or during the study period, as well as severe visual and cognitive impairments that could interfere with treatment/testing, usual contraindications to MRI (Metal implants, etc.), and parent(s) unable/inapt to provide consent for their child's participation. Based on their current list of children followed in each centres, there will not be any issue to recruit these group children in the 4 investigating centres of the project.

### *Design and Randomization*

This project will involve **2 single-blind randomized controlled trials (RCTs), one with children with unilateral CP and the other with children with bilateral CP**. The decision to carry out two separate RCTs was made by the consortium and methodologist based on the fact that the causes, and most importantly for this project, the functional motor outcomes and rehabilitation goals differ for these two CP types. For each RCT, the randomisation will be carried out 24 hours per day using centralised computer randomisation by internet. A **pair-matched randomization** will be used in order to ensure comparability. For children with unilateral CP, each child will be matched with a child with the closest profile based on age (4 categories: 1,2,3,4 yo), the affected side (right or left), and the origin of the CP (prematurity, perinatal asphyxia, stroke, others). For children with bilateral CP, each child will be matched with a child with the closest profile based on age (4 categories: 1,2,3,4 yo), the Gross Motor Function Classification System level (GMFCS, 3 categories: I-II, III-IV and V) and the origin of the CP (prematurity, perinatal asphyxia, stroke, others). All the efforts will be made in both RCTs to find the closest profile within the same year, same GMFCS level and same origin of CP. Group allocation will be then randomly determined within each pair. This design was chosen to limit the heterogeneity in clinical pattern between the intervention and control arms, while keeping the benefit of individual randomization. It is commonly used and widely accepted in the field of neuropsychiatric rehabilitation. The 2 trials will also be equilibrated according to the age groups 1-2 (50% of the group) and 3-4 (50% of the group) in order to investigate the effect of window of opportunity.

In both RCTs (unilateral and bilateral), the children will be randomized to receive HABIT-ILE or the Control condition. The children in the control group will receive the therapy after the 3 month follow-up assessment in order to decrease drop-out at follow-up in this group, however, this will not be included in the analysis. Thus the between group comparisons will be carried out between T0 and T+15 and between T0 and T+90. The design of RCTs 1 and 2 is presented in Annex.

The HABIT-ILE group (unilateral n=25/bilateral n=25) will receive 50 hours of treatment over 2 weeks (5 hours per day of treatment, 5 days a week) whereas the control group (unilateral n=25 /bilateral n=25) will follow their usual activities for 2 weeks (nursery, usual therapy etc.).

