### *Evaluation criteria*

In each RCT, both groups (N=25) will be assessed 3 times: T0, T+15 days and T0+90 days (See study design in Figure 4).

For the RCT 1, the primary outcome measure will be the difference in the **Assisting Hand Assessment (AHA, from 18 months to 18 years) or Mini Assisting Hand Assessment** (Mini-AHA, from 8 to 18 months) between T0 and T0+90 days. It quantifies through a Rasch analysis the assistance that the more affected hand can provide to the less affected hand in bimanual activities. This primary outcome was chosen because 1) it has become the gold standard measure of bimanual performance in children with unilateral CP 2) its **responsiveness, reliability and validity** have been demonstrated in children with CP including infants and toddlers. 3) its raw scores are transformed through a rash-model into linear measures, allowing the use of parametric statistics 4) the assessment can be **videotaped and scored by a trained examiner totally blind** to group assignment and timing of assessment ensuring a blind scoring, which is planned for this study. The minimal detectable change is 4 AHA-Units (0.97 logits).

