improvement could reach at the most 5 logits. Then, we hypothesize a difference between both groups of 5 logits and a SD of improvement of 5 logits with an  $\alpha=0.05$  and a  $1-\beta=0.9$ . With these hypothesis, a sample size of 23 participants per group is required, with a total of 46 participants. Considering potential drop-outs, **50 participants will be included in total.**

Improvements in GMFM and AHA will be compared between study groups using analysis of covariance (ANCOVA) to adjust for baseline measurement (as described and recommended in Vickers et al.) Non-parametric methods will be performed whenever ANCOVA assumptions (homoscedasticity, normality) are not met. Age-subgroup (or according to other characteristics) and interaction analyses will be performed for exploratory purpose. As recommended by Good Clinical Practice, exploratory analyses will be used for hypothesis generating but cannot be conclusive alone. The statistical analysis of the secondary outcome measures are described in the relevant WPs. Secondary outcome analysis, as well as subgroup analysis, should be considered as exploratory unless using specific methods in order to control the Type I error probability (multiplicity problem).

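### RCT1 matches on whole years of age, so the 1-year category spans the 18-month change from Mini-AHA to AHA, and neither the matching nor the stated ANCOVA accounts for the instrument

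*Protocol*

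**What the plan says.** - **Eligibility** (Protocol 2.3, Participants): "age 1 to 4 years inclusive (corrected age if preterm birth"). Children of 12 to 17 months can therefore enter.
- **Matching in RCT1** (Design and Randomization): "age (4 categories: 1,2,3,4 yo), the affected side (right or left"), together with origin of the cerebral palsy. The closest age match that the text commits to is the same year: "All the efforts will be made in both RCTs to find the closest profile within the same year, same GMFCS level and same origin of" (last word omitted).
- **Allocation** (same section): "Group allocation will be then randomly determined within each pair". Each trial is also to be "equilibrated according to the age groups 1-2 (50% of the group) and 3-4 (50% of the group").
- **Primary outcome of RCT1** (Evaluation criteria): the change on the "AHA, from 18 months to 18 years) or Mini Assisting Hand Assessment", the latter given as "Mini-AHA, from 8 to 18 months) between T0 and T0+90 days". The minimal detectable change is stated in AHA units only. The section does not say whether the two versions report on one common scale.
- **Analysis** (Statistical analysis): "analysis of covariance (ANCOVA) to adjust for baseline measurement". No term for instrument is named.

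**The concern.** The protocol pairs children so that the arms are comparable. In the youngest year, the age category and the instrument boundary do not line up. A child of 13 months assessed with the Mini-AHA and a child of 22 months assessed with the AHA count as an exact age match.

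If the two versions do not share a scale, or if children under and over 18 months change by different amounts, two things follow. Chance differences between arms in the number of Mini-AHA children add noise to the primary comparison. In addition, a single baseline adjustment across both versions leaves variance that could have been removed.

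The point stands even if every child keeps the same version at T0 and T0+90 days. A child who passes 18 months during follow-up raises a separate question.

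**Working it through.** **1. The plan's own figure.** For RCT1 the protocol uses a standardised effect of 1 SD, alpha 0.05 and power 0.90, and states 23 per group. A two-sided t-based calculation gives 22.02, rounded up to 23, so the figure reproduces. Nothing below changes it.

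**2. How many children are concerned.** Half of 50 are to be aged 1-2, which is 25. If half of those are aged 1 (assumption), there are about 12, or 6 pairs. If ages are evenly spread over 12 to 24 months (assumption), half of them, about 6, are under 18 months at T0.

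**3. Mixed pairs.** Let p be the share of one-year-olds under 18 months.
- *Random pairing within the category:* P(mixed) = 2p(1-p). At p = 0.5 this is 0.50, so 6 x 0.50 = 3 mixed pairs are expected. For p of 0.25 or 0.75 it is 0.375, so 6 x 0.375 = 2.25.
- *Strict nearest-age pairing, ignoring side and origin:* with the 12 children sorted by age, at most one pair can cross 18 months, and only if the number below it is odd. That has probability 0.5, so 0.5 mixed pairs are expected.

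**4. Imbalance between arms** (12 one-year-olds, p = 0.5).
- *Random pairing:* the difference in Mini-AHA counts is distributed as Binomial(12, 0.5) - 6. P(difference of 2 or more) = 1 - (792 + 924 + 792)/4096 = 1 - 2508/4096 = 0.39. The mean absolute difference is 1.35 children.
- *Nearest-age pairing:* the difference cannot exceed 1, so this probability is 0.

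Over 6 to 24 one-year-olds, random pairing gives 1.5 to 6 mixed pairs and a probability of 0.22 to 0.54.

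**5. Effect on the estimate.** Let d be the difference in mean change between instruments. The protocol gives no value for d. An imbalance of 2 in 25 shifts the arm difference by (2/25) x d. With the pilot SD of 6.7 and 25 per arm, the standard error of the difference is 6.7 x sqrt(2/25) = 1.9.

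| d (assumed, units) | shift (units) | in standard errors |
|---|---|---|
| 0 | 0 | 0 |
| 2 | 0.16 | 0.08 |
| 5 | 0.40 | 0.21 |
| 8 | 0.64 | 0.34 |

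At d = 5 the shift is a tenth of the 4-unit difference (6 versus 2) in the eco-CIMT trial used for planning. At the mean imbalance of 1.35 it is (1.35/25) x 5 = 0.27 units.

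**6. Residual variance.** With 6 of 50 on the Mini-AHA and d = 5, the added variance is 0.12 x 0.88 x 25 = 2.6, against 6.7 squared = 44.9, or about 6%.

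**7. Cost of a rigid split at 18 months.** Two sides by four origins make 8 cells for 12 one-year-olds. A split makes 16. With k equally likely cells (assumption), the expected number of exactly matched pairs is k x [12/k - P(odd)]/2, where P(odd) = [1 - (1 - 2/k)^12]/2.
- k = 8: P(odd) = 0.484, giving 4.1 of 6 pairs.
- k = 16: P(odd) = 0.399, giving 2.8 of 6 pairs.

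**The case against.** Most of the case on the other side stands and sets the limits of the point.

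- **Bias.** A reader might infer that the primary estimate is biased. It is not. Allocation is random within pairs, so any imbalance in instrument is chance and is already reflected in the standard error.
- **Incomparable scores.** A reader might infer that the two versions yield scores that cannot be compared. The protocol describes both under one Rasch-based account and does not describe the items of either. It supports neither that claim nor its opposite. If the scales are common, only differences in change with age remain.
- **Pair contrasts.** The stated analysis compares groups, not pair-mates. A mixed pair is a looser match, not a faulty comparison.
- **Three mixed pairs as the expected result.** That figure is one end of a range. The protocol asks for the closest profile, and staff who look at months of age could come near the other end. The text does not require this, however, since age is defined in whole years.
- **Variance.** The pilot children were aged 1 to 4 years, so the pilot SD may already contain this source of spread. The planning effect was also lowered from 1.26 to 1 out of caution about variability.
- **Place in the documents.** An instrument term in the model may be in a statistical analysis plan that is not at hand. The matching rule is fixed in the protocol, so that part of the objection does not remove the point.

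**Conclusion.** The mismatch is real and follows from the protocol's own text: eligibility from 12 months, matching by whole year and a change of instrument at 18 months. It is a minor, optional improvement. The loss is one of balance and precision, confined to about a quarter of RCT1 if ages are even.

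Under the assumptions of 12 one-year-olds with evenly spread ages, 0.5 to 3 of 6 pairs would be mixed, and the chance of an imbalance of two or more lies between 0 and 0.39. The consequence for the estimate rests on a difference between instruments that the protocol does not give. At an assumed 5 units it is about 0.2 standard errors. The sample size of 23 per group is unaffected.

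A separate category boundary at 18 months may look like the natural remedy. It would reduce exact matches on side and origin noticeably (4.1 to 2.8 of 6 pairs in the calculation above), and the size of the problem does not justify that.

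**What to change.** 1. **Matching (RCT1, Design and Randomization).** Keep the present categories. Add that, among candidates equally matched on side and origin, the partner nearest in months of age is chosen, on the same side of 18 months where possible.
2. **Analysis (RCT1).** Add a single indicator for the instrument used at T0 to the ANCOVA, in the protocol or in the statistical analysis plan if it is not already there. It is fixed before allocation, so it is well defined even for a child who passes 18 months by T0+90 days. Do not fit a separate baseline slope, which would rest on about 6 children.

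It would also help to state whether Mini-AHA and AHA results are reported on one scale.

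Cost: one degree of freedom and a slightly more detailed matching rule. Both changes use data that are already collected. They reduce mixed pairs but do not exclude them, since no suitable partner may be available.
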